## Results

The study was funded in October 2023 and is still in progress. Enrollment and data collection began in October 2023, and we aim to cover 200 patients by mid-2026. A second inclusion center is planned to be opened by mid-2025. Data analysis will start in June 2026, and the results are expected by the end of 2026.

## Discussion

### Summary

This study protocol aims to evaluate the risk of AF in patients with BC who have undergone RT, addressing a critical gap in understanding cardiovascular complications of BC treatment. AF is a common arrhythmia with potential to cause severe complications, and its risk may be heightened by the incidental cardiac radiation exposure during RT for BC. Given the increasing survival rates in patients with BC, assessing long-term cardiovascular outcomes has become essential for optimizing post-treatment care.

Several studies have investigated the association between RT for BC and AF [6,26,62]; however, these studies have not provided precise dosimetry data for cardiac substructures, and it remains unclear whether this association is causative or whether cancer and AF just share the same pathophysiologic mechanisms. Our study aims to enhance our understanding of how radiation dose distribution across specific cardiac regions correlates with AF incidence. Our study’s approach involves detailed dosimetry analysis of cardiac substructures using deep learning–based autosegmentation, including the left and right atria, the left and right ventricles, coronary arteries, the conduction system, and PVs. This precision in quantifying radiation doses received by these areas will allow for a more granular assessment of radiation exposure and its impact on AF risk, distinguishing our study from studies that have evaluated whole-heart doses [26]. Univariate and multivariable regression analyses will be used to isolate the effects of these localized radiation doses, while adjusting for confounding factors, such as age, comorbidities, and chemotherapy. This will provide an understanding of the dose-response association and help identify high-risk cardiac regions.

With a retrospective design, previous studies that have investigated AF occurrence in patients with BC may have undercaptured AF events, particularly in the case of silent AF. Traditional methods, such as standard ECGs and echocardiography, have proven efficacy in detecting AF but often lack continuous monitoring capability essential for capturing transient AF episodes. Smartwatches, equipped with SL-ECG recording, offer a promising adjunct, providing continuous real-time data on heart rhythm. To investigate AF incidence over 5 years post-RT, our study combines retrospective patient-reported outcomes and cross-sectional screening based on smartwatches, in addition to traditional diagnostic methods (ECG and echocardiography). Patient questionnaires capture symptoms and medical history, offering a broader context for interpreting cardiovascular health and identifying potential noncardiac factors influencing AF risk. ECG and echocardiography will provide objective data on cardiac rhythm disturbances and structural and functional cardiac abnormalities. More particularly, in patients with AF, echocardiography will allow us to investigate the underlying etiology and assess the risk of complications, while patients’ medical records will provide information about the timing and risk factors for the occurrence of AF and other arrhythmias/conduction disorders during the 5 years following RT. This multimodal approach will allow for a comprehensive understanding of AF development in the context of radiation exposure and patient-specific factors.

### Limitations

However, this study presents several limitations. First, the sample size is relatively small, which, although suitable for an exploratory analysis, will limit the generalizability of our findings. Future studies should incorporate larger cohorts to enhance the statistical power and validity of the results. Due to the inclusion criteria, which selected only patients aged more than 65 years and who own and are able to use multiple digital tools (smartphone, smartwatch, email) or at least be assisted by a caregiver, our estimates of AF at the scale of our population will not be applicable to all patients with BC. However, results on the association between cardiac radiation exposure and AF will not be biased by such potential selection bias. Moreover, this exploratory study does not intend to provide exhaustive figures of AF in all patients with BC who are >65 years old, but it will compare AF between high- and low-cardiac-exposure groups. Selection bias, if any, will not be impacted by the cardiac radiation exposure level of patients. Thus, our study should not provide biased results regarding the potential association between cardiac radiation exposure and AF risk. Second, the study population is limited to older adults, potentially overlooking age-related variability in radiation-induced AF risk. Expanding the research to include a broader age range will provide a more comprehensive understanding of the age-dependent effects. Third, for retrospective collection of medical data, some patients may provide incomplete information, resulting in missing data. However, this issue will be limited by additional collection of missing data based on medical records. Last, the follow-up period is limited to 5 years and AF screening performed 5 years after RT. Missed screening of AF should be limited by a combination of retrospective and cross-sectional design. The retrospective part will allow us to collect data on the occurrence of AF based on patients’ questionnaires and medical records for a duration of 5 years post-RT. In cross-sectional screening 5 years after RT, patients will wear their smartwatch for a duration of 1 month. This duration will not avoid missed screening for patients with AF that would not occur during this period. Moreover, this duration and opportunistic single-timepoint screening may not fully capture the long-term incidence of AF or the shorter effects post-RT, suggesting the need for both shorter-term and extended follow-up in future investigations to better understand the timing and progression of AF posttreatment.

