## Introduction

### Background

Breast cancer (BC) is the most common cancer in women [1]. Early screening and advances in treatment, including surgery, chemotherapy, hormone therapy, and targeted therapies, have significantly improved survival rates. Radiotherapy (RT) plays a crucial role in BC management by reducing the risk of local recurrence and improving overall survival, particularly following breast-conserving surgery [2]. Despite its efficacy, RT for BC can induce adverse effects on the heart, particularly when the heart is near the radiation field. Cardiac complications can include coronary artery disease, pericarditis, valvular heart disease, and myocardial infarction [3-5]. Emerging evidence also indicates a risk of atrial fibrillation (AF) in patients with BC that may manifest months to years after treatment [6,7]. AF is a common cardiac arrhythmia characterized by an irregular and often rapid heart rate [8,9] that can eventually lead to conditions with significant health impacts (stroke, heart failure, dementia) [10-12]. AF screening is challenging, further compounded by its frequent asymptomatic nature, which has often gone undetected in retrospective noninterventional studies. It is therefore crucial to further investigate the risk of AF in patients with BC as it may compromise the quality of life and survival of patients.

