### Relationship Between Cardiac Exposure to Radiation and Atrial Fibrillation Among Patients With Breast Cancer

Women treated with RT for BC present clinical characteristics at baseline that may induce a higher risk of cardiac events independent of irradiation, and it is consequently crucial to consider cardiac dosimetry to better understand the potential association between RT and the occurrence of AF and then establish a causality link. The association between the mean heart radiation dose and AF risk have been poorly investigated. The Northern Ireland Cardiac Health Events After Radiotherapy (NI-HEART) Study of patients with lung cancer found a dose-response relationship with HR=1.75 (95% CI 1.03-2.97) [45]. For BC, a similar association with the mean heart radiation dose was observed, with HR=1.23 (95% CI 1.15-1.32) [46]. However, radiation exposure of the heart during RT is not homogeneous, and the mean heart radiation dose is often not relevant to evaluate cardiac substructure RT doses [47] that may be more relevant to evaluate associations with AF. Some studies have begun to explore the dosimetry of cardiac substructures, and recent data have demonstrated associations between cardiac substructure radiation doses and specific cardiac events or mortality in patients. In a cohort that included 238 patients with esophageal cancer treated with RT, increasing the mean left atrial radiation dose was associated with AF risk (with 30% for every 10 Gray increase) [48]. In the field of arrhythmias and conduction disorders, this was observed for the right atrium and the sinoatrial node and the risk of conduction disorders in patients with BC [49-51]. In the case of AF, the arrhythmogenic tissue is often located in the pulmonary veins (PVs), but these structures are not yet considered organs at risk during RT planning, despite a potential relevant association, as suggested in the NI-HEART Study, which investigated the PV radiation dose and the risk of AF in patients with lung cancer following RT. Dose metrics for both the left (V55) and the right (V10) PVs were associated with the incidence of new AF (HR 1.02, 95% CI 1.00-1.03, *P*=.005, and HR 1.01, 95% CI 1.00-1.02, *P*=.033, respectively) [52]. Further research is needed to accurately assess the radiation doses absorbed by some of these substructures and to determine whether the exposure of certain potentially critical structures can better predict the risk of cardiac arrhythmias, particularly AF, in patients with BC. Indeed, identifying critical substructures for AF in women undergoing RT for BC and demonstrating the dose-risk relationship could thus improve RT delivery protocols to limit the occurrence of these arrhythmias.

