### Study Population

In this study, we plan to include 200 female patients with unilateral BC, aged over 65 years old at inclusion and treated at least 5 years ago with postoperative modern photon-based RT after surgery. For this study, we will focus on patients aged >65 years, as recommended by the European Heart Rhythm Association [43], which concluded that systematic screening using intermittent ECG may be beneficial to detect AF in individuals aged >65 years with comorbidities increasing the risk of stroke. Patients with a history of cancer or AF before RT or with recurrent cancer (BC or other) after RT will be excluded. Inclusion and exclusion criteria are summarized in Textbox 1.

Inclusion and exclusion criteria.

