**Inclusion criteria:**
Women surgically treated for left or right breast cancer (BC) and for whom adjuvant treatment is radiotherapy (RT), with irradiation of the breast or chest wall irradiation and possibly ganglion chainsAdjuvant RT performed between 5 years before enrollmentA 5-year post-RT follow-up oncologist consultation performed in one of the investigating centersAge 65 years or more at enrollmentOwning a smartphone and able to understand and use digital tools alone or with the help of a caregiverConsented to a connected follow-upAffiliated with a social security system or equivalentVolunteering to participate in the study and providing signed informed consent

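### The Limitations section rules out selection bias in the dose-AF association, but enrolment requires survival to the 5-year visit, which the protocol's own Introduction links to both cardiac dose and AF

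*Protocol article*

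**What the plan says.** The Limitations section concedes that the age and digital-tool criteria restrict how far the AF estimates apply. It then says that "results on the association between cardiac radiation exposure and AF will not be biased by such potential selection bias". In that sentence the bias meant is the one from age and digital criteria. The section goes on in general terms: "Selection bias, if any, will not be impacted by the cardiac radiation exposure level of patients". From this it concludes that the study should not give biased results on dose and AF. It offers no argument or data, and it does not mention death before the 5-year visit.

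Textbox 1 and Study Population set the conditions for entry:
- a "5-year post-RT follow-up oncologist consultation performed in one of the investigating" centre;
- no new cancer, since patients "with recurrent cancer (BC or other) after RT will be excluded";
- being "able to understand and use digital tools alone or with the help of" a caregiver.

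The primary outcome (Outcome Measurement) is the difference in AF occurrence over the 5 years after radiotherapy between women at or above the 75th percentile of whole-heart dose and women below it.

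The Introduction bears on survival in two places. On exposure, the section on cardiac exposure and AF says that "recent data have demonstrated associations between cardiac substructure radiation doses and specific cardiac events or mortality in patients". On outcome, the Background says of AF that "it may compromise the quality of life and survival of patients".

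**The concern.** Exposure happens at year 0, AF is counted over years 0 to 5, and women are enrolled at about year 5. Anyone who died in between is absent, whatever her dose and whatever her AF history. If dose and AF both influence survival, as the Introduction suggests, the enrolled women can show a different dose-AF association from all the women treated.

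What is at stake is how a weak or null result is read. The Abstract and the Conclusion say the findings should inform radiotherapy delivery and prevention. A small difference presented as free of selection bias could reassure more than this design can justify.

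**Working it through.** **1. Passages side by side.** The Limitations section needs selection to be unrelated to cardiac dose. Textbox 1 makes attendance at a 5-year visit a condition of entry, so survival is one too. The Introduction ties substructure dose to mortality and AF to survival. The text that motivates the study therefore does not support the no-bias statement.

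**2. Inputs for an illustration.** The disputed sentences contain no figure to reproduce. The AF risks come from Sample Size Calculation: 25% at high dose and 10% at lower dose. The 75th-percentile cut splits 200 women into 50 and 150. Tests are two-sided at 5% (Planned Statistical Analysis). The documents give no enrolment probabilities, so those below are **assumptions**.

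The true odds ratio (OR) is (0.25/0.75)/(0.10/0.90) = 3.00 and the true difference is 15.0 points. Power at 50/150 (normal approximation, pooled variance) is 72.7%. The shortfall from the stated 80% is a separate matter, as is the Abstract's 15% for the lower-dose group.

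**3. Formulas.** Let r be the enrolment probability with AF divided by that without AF, within a dose group.
- Observed risk = p·r / (p·r + 1 − p)
- Observed OR = true OR × (r at high dose / r at lower dose)

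Example with r = 0.8 in both groups:
- High dose: 0.25 × 0.8 / (0.20 + 0.75) = 0.20/0.95 = 21.1%
- Lower dose: 0.10 × 0.8 / (0.08 + 0.90) = 0.08/0.98 = 8.2%
- OR = 3.00 × 0.8/0.8 = 3.00; difference 12.9 points

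**4. Results.**

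| Assumed r (high / lower dose) | Observed risks | Difference (points) | OR | Power at 50/150 |
|---|---|---|---|---|
| 1.0 / 1.0 (no selection on AF) | 25.0% / 10.0% | 15.0 | 3.00 | 72.7% |
| 0.8 / 0.8 | 21.1% / 8.2% | 12.9 | 3.00 | 67.0% |
| 0.8 / 0.9 | 21.1% / 9.1% | 12.0 | 2.67 | 59.7% |
| 0.7 / 0.9 | 18.9% / 9.1% | 9.8 | 2.33 | 47.3% |
| 0.6 / 0.9 | 16.7% / 9.1% | 7.6 | 2.00 | 33.7% |
| 0.9 / 0.8 | 23.1% / 8.2% | 14.9 | 3.38 | 76.3% |

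**5. Reading the table.**
- Selection on dose alone leaves r at 1 in both groups, so neither measure moves (first row).
- Selection that is multiplicative in dose and AF leaves the OR at 3.00 but still shrinks the risk difference (second row).
- The OR moves only when the AF effect on enrolment differs by dose. It falls if the loss is greater at high dose (rows 3 to 5) and rises if it is greater at lower dose (last row).

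**The case against.** The strongest defence is that selection on dose, on AF, or multiplicatively on both leaves the odds ratio intact. That stands for the OR. It does not rescue the categorical statement: the protocol does not show that selection is multiplicative, and the primary outcome is worded as a difference in occurrence, which moves even when the OR does not.

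Several stronger readings are tempting, and the documents do not support them:
- **The association is understated.** A reader might infer this from women with AF dying early. It is plausible, but the direction depends on how AF-related loss differs by dose, which is unknown.
- **The recurrence exclusion is a further biasing path.** The Background says only that radiotherapy lowers local recurrence, and every participant had radiotherapy. Nothing links heart dose or AF to recurrence.
- **The digital criterion selects on AF.** The Background lists stroke and dementia as consequences of AF, but the step to digital ability is an inference, and caregiver help is allowed.
- **Radiotherapy's known cardiovascular and cerebrovascular effects prove the point.** Those statements concern radiotherapy itself. The contrast here is higher against lower dose among women who were all irradiated, so only the dose-mortality statement is relevant.

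It is also fair to say that the study calls itself exploratory, and that a flow table or sensitivity analysis may sit in documents not shown. Their absence is not the finding. The finding is a statement the article makes.

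**Conclusion.** Wrong as written, in a limited sense. The no-bias statement claims a property that this design does not have, and it conflicts with the Introduction on one path, survival to the 5-year visit. The supportable statement is that the dose-AF association may be biased by survival to enrolment. The size is unknown and the direction is not established, with understatement plausible.

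The figures above show how the mechanism works and are not an estimate of bias in this study. They rest wholly on assumed enrolment probabilities. No eligibility rule, endpoint or planned test is shown to be wrong. What changes is how far a weak or null association may be interpreted.

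**What to change.** 1. Withdraw the sentences in Limitations that declare the dose-AF association free of selection bias.
2. State that the results apply to recurrence-free 5-year survivors who volunteer and can use the devices alone or with a caregiver.
3. Name survival to 5 years as a possible source of bias in the dose-AF association, of unknown size.
4. Where access to treatment records permits, tabulate all women treated in the same window by heart-dose group, or by laterality if dose is unavailable: enrolled, declined, died, recurred, lost.
5. Add a bounding analysis that divides the observed OR by a range of assumed ratios of AF-dependent enrolment (high over lower dose), and converts risks in the same way. Inverse-probability weights built only on age, side and dose would not do this: within a dose group they do not depend on AF, so they cannot restore cases lost because of AF.

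The cost is a less favourable limitations paragraph, one table and one short sensitivity analysis. Aggregate data on non-participants may need a data-protection check. If access is refused, items 1 to 3 still stand and need no new data.

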
### Conclusion

To conclude, this study will refine our understanding of radiation-induced AF after RT, a topic almost absent from the European Society of Cardiology (ESC) guidelines on cardio-oncology [63]. Given the relatively high incidence rate of AF from a certain age in the general population, identifying increased AF risk linked to RT could result in a significant number of RT-attributable cases. Detecting silent AF may necessitate medical/preventive management for certain patients to limit the risk of stroke. The use of smartwatches has never been studied in a specific population, such as patients treated with RT for BC. This study will evaluate the interest of patients and cardiologists in this type of connected tool within this population. The results of this project could provide recommendations for primary and secondary prevention strategies to limit RT sequelae and improve patients’ quality of life.

## Appendix

Multimedia Appendix 1 Medical questionnaire: list of items; cardiology consultation: list of items; and questionnaire to evaluate patient satisfaction with and usability of the smartwatch integrated with electrocardiogram (ECG) recording.

## Abbreviations

AF: atrial fibrillation
AI: artificial intelligence
BC: breast cancer
CT: computed tomography
ECG: electrocardiogram
HR: hazard ratio
NI-HEART: Northern Ireland Cardiac Health Events After Radiotherapy
PV: pulmonary vein
PV: pulmonary vein
RT: radiotherapy
SL-ECG: single-lead electrocardiogram
SUS: System Usability Scale
TTE: transthoracic echocardiography
WATCH: Watch Your Heart After Radiotherapy for Breast Cancer
